### Randomization and blinding

This study has a single-blind design. Patients will be unaware of their group allocation, which will only be known to the lead investigator and acupuncture physician. The randomization sequence and allocation ratio (1:1:1:1:1:1) will be generated using the statistical software SPSS 26.0. Group allocation will be concealed using opaque envelopes, which will be distributed sequentially after patient enrolment.

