**Methods and analysis:**

A total of 560 patients will be recruited and randomly allocated to receive one of the following seven interventions: continuous wave EA, continuous wave TEAS, continuous wave TEAS + EA, dilatational wave EA, dilatational wave TEAS, dilatational wave TEAS + EA, and a control. For this study, continuous waves at 2 Hz, and dilatational waves at 2/50 Hz would be selected. The points to be stimulated by EA are the bilateral Neiguan (PC6), Hegu (LI6), Zusanli (ST36), Shangjuxu (ST37), and Xiajuxu (ST39), and TEAS would stimulate the bilateral Liangmen (ST21) and Daheng (SP15). The control group will neither receive EA nor TEAS. All patients will undergo an enhanced recovery plan after surgery and be provided with standardized perioperative management. Treatment will start on the first postoperative day and be administered once daily in the morning until the patient regains spontaneous bowel movements and can tolerate oral intake of solid food. The primary outcome is a composite of time to first defecation and time to tolerance of a solid diet. Secondary outcomes include time to first exhaustion; time of first defecation; time of tolerance of a solid diet; time to the first ambulation; length of hospital stay from surgery to discharge; visual analog scale score for postoperative daily pain, nausea, and vomiting; incidence of postoperative complications; and treatment acceptability.

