## Methods and analysis

### Study design

This is a prospective, single-center, parallel, single-blind, randomized controlled trial. Effectiveness and safety will be compared among three acupoint stimulation methods (EA, TEAS, TEAS+EA) and two EA instrument waveforms (continuous waves, dilatational waves) to determine their suitability for promoting them in postoperative rehabilitation. This study will be conducted in accordance with the principles of the Declaration of Helsinki. The “Standard Protocol Items: Recommendations for Interventional Trials” checklist is provided in Supplementary Material 1.

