#### Control group

Only ERAS-standardized perioperative management, without TEAS or EA, will be performed in the control group.

All acupoints will be routinely disinfected. The acupoints in the distal limb will be punctured straight through the skin to a depth of 25–30 mm using disposable stainless steel needles (0.25 × 40 mm, Suzhou Jiajian, Jiangsu, China). The needle will then be twisted slightly to achieve the de qi sensation, and the EA apparatus will be connected with a set of electrodes in the ipsilateral Neiguan (PC6), Hegu (LI4), Zusanli (ST36), and Xiajuxu (ST39). The abdominal acupoints will be stimulated with a self-adhesive electrode sheet with electrical conductivity, and the ipsilateral Liangmen (ST21) will be connected with a set of electrodes at Daheng (SP15).

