### Limitation

This trial will not include a sham control arm, and a placebo response and effect analysis is lacking. Nevertheless, some studies on the use of acupuncture for gastrointestinal symptoms have shown that EA may have more significant benefits than sham acupuncture, despite a placebo effect (36, 37).

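### Patients are said to be unaware of their allocation, but the arms differ visibly and there is no sham, so patient blinding is possible for only 3 of the 21 arm comparisons

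*Protocol article*

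**What the plan says.** The Study design section describes a "prospective, single-center, parallel, single-blind, randomized controlled trial". Randomization and blinding repeats the label ("This study has a single-blind design") and explains it: "Patients will be unaware of their group allocation, which will only be known to the lead investigator and acupuncture physician". Neither sentence is limited to particular arms or comparisons.

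According to the Abstract, patients are "randomly allocated to receive one of the following seven interventions". These are three stimulation modalities, each with two waveforms, plus a control. The Intervention subsections and the paragraph on technique under Control group describe what patients experience:

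- **Control:** "Only ERAS-standardized perioperative management, without TEAS or EA, will be performed in the control group".
- **EA:** distal limb points are "punctured straight through the skin to a depth of 25–30 mm using disposable stainless steel needles", and then: "The needle will then be twisted slightly to achieve the de qi sensation".
- **TEAS:** adhesive conducting pads on four abdominal points.
- **TEAS+EA:** both of these.

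In every active arm the current is raised to what the patient tolerates, and a session lasts 30 minutes each morning. Under Limitation the article says: "This trial will not include a sham control arm". It adds that placebo effects are not analysed.

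**The concern.** A patient given perioperative care alone knows that no needles or pads were applied. A patient with needles in the arms and legs can tell this from pads on the abdomen, and either can be told from having both. No masking procedure is described, and none applied to the active arms could hide from controls that they received nothing. The unqualified statement that patients do not know their group therefore conflicts with the treatments the article specifies.

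What is at stake is how the comparisons may be read. One component of the primary outcome, tolerance of solid food, depends partly on the patient's willingness to eat and on judgement. VAS pain and nausea and treatment acceptability are the patient's own report. First ambulation and discharge depend on behaviour and staff decisions. Active patients also receive a daily session of attention that controls do not. A single-blind label tells readers and risk-of-bias assessors that patient expectation has been controlled, when for most comparisons it has not.

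**Working it through.** **1. The plan's own figure.** The Sample size section gives 80 per arm and 560 in total (two-sided α 0.05, 90% power, 20% dropout) without naming a formula. The smallest active-versus-control difference in the pilot data is cTEAS against control: 110.8 − 86.8 = 24.0 h. The root-mean-square SD is √[(40.1² + 42.3²)/2] = 41.2 h. Then n = 2(1.960 + 1.282)² × 41.2² / 24.0² ≈ 62 per arm, or 63 with the noncentral t. Dividing by 0.8 gives 78 to 79 per arm, or 546 to 553 in total, close to the stated 560. The blinding point does not alter this number.

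**2. Classify the arms by what the patient receives.**

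- Nothing: control (1 arm)
- Limb needles: cEA, dEA (2 arms)
- Abdominal pads: cTEAS, dTEAS (2 arms)
- Both: cTEAS+EA, dTEAS+EA (2 arms)

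**3. Count the pairs.** The total is 7 × 6 / 2 = 21.

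| Type of pair | Count | Can the patient be blind? |
|---|---|---|
| Active against control | 6 × 1 = 6 | No |
| Active against active, different modality | 3 modality pairs × 2 × 2 = 12 | No |
| Same modality, different waveform | 3 | Yes, feasible |

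So 6 + 12 = 18 pairs are distinguishable to the patient. The remaining 3 (cEA/dEA, cTEAS/dTEAS, cTEAS+EA/dTEAS+EA) differ only in 2 Hz against 2/50 Hz.

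**4. Set this against power.** I used the pilot means and SDs, 80 × 0.8 = 64 evaluable patients per arm, and an unadjusted two-sided 5% t-test. The article plans Student–Newman–Keuls comparisons, so these values are indicative.

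- The 3 maskable pairs have 15% (EA), 12% (TEAS) and 15% (TEAS+EA) power.
- The 6 pairs against control all have at least 90%; the lowest is cTEAS at 90.5%.
- One between-modality pair also passes 90%: cTEAS against dTEAS+EA, difference 86.8 − 64.1 = 22.7 h, SD 38.25 h, power 91.5%. Next is cEA against dTEAS+EA at 89.4%.

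On the pilot figures, every comparison that reaches 90% power is therefore one in which the patient can tell the treatments apart.

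**5. Scale of a possible bias (assumed values only).** The article gives no estimate of an expectation effect. Suppose there is no true effect, the SD is 42.3 h (control arm), there are 64 evaluable per arm, and the same unadjusted test is used. The chance of a significant difference from control would be:

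| Assumed bias in the primary outcome | Chance of p < 0.05 |
|---|---|
| 0 h | 5% |
| 5 h | 10% |
| 10 h | 26% |
| 15 h | 51% |
| 20 h | 76% |

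The table shows sensitivity. It does not estimate what will happen in this trial.

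**The case against.** The strongest reply is disclosure. The Limitation section states that there is no sham and that placebo effects go unanalysed, and the Control group section says plainly that controls receive no stimulation. A careful reader can see that non-specific effects are not separated out. That stands as far as it goes, and the missing sham is an acknowledged design choice. But the Limitation section does not withdraw or qualify the statement that patients are unaware of their group, so the contradiction remains.

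The second reply is that patient blinding is not wholly absent. Waveform is one of the two factors the trial compares, and patients who know their modality may still not know their waveform. This is correct. A reader might infer that the single-blind property is simply false; the documents support only that it is stated too broadly.

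Third, time to first defecation is a discrete event and less open to expectation than diet tolerance or a VAS score. This also stands. The article does not say how the two components of the primary outcome combine, so no fixed share of it can be called soft.

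Fourth, a condensed article may leave detail to the full protocol. That covers matters such as a written criterion for tolerating solid food or analysis with coded arms, and I make no point of their absence. It does not cover a positive statement that the article's own treatment descriptions contradict.

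**Conclusion.** The blinding statement is wrong as written and must be corrected. Patient blinding cannot hold for 18 of 21 comparisons, including all 6 against control; it is feasible for the 3 waveform comparisons within a modality. The count follows directly from the arm descriptions. It rests on one assumption: that patients, having given informed consent, know broadly what the other arms involve. Even if they did not, what they experience and the attention they receive would still differ between arms.

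The consequence is a risk of bias whose size and direction the article does not allow one to derive. Two stronger readings are not supported. A reader might infer that the trial's conclusions against control are overstated, but this is a protocol with no results or conclusions to overstate. A reader might also infer that the control comparisons are the only ones with 90% power. The Sample size section does not tie its power to any contrast, and on its pilot figures cTEAS against dTEAS+EA reaches about the same level.

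**What to change.** 1. In Study design and in Randomization and blinding, limit the patient-blinding statement to waveform within a modality. Describe the comparisons with control and between modalities as open-label to the patient.
2. State, in the Limitation section or with the analysis, that effects against control combine stimulation with attention and expectation on top of ERAS care.
3. The article already confines knowledge of allocation to two roles. Apply that restriction explicitly to the existing ward staff who record outcomes, as far as practicable. The article does not say who records the efficacy outcomes, so this assumes it is ward staff.

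The cost is revised wording and an instruction to existing staff. The design label becomes less favourable, and masking of ward staff will be imperfect because needles and pads are visible and patients may talk. No sham arm, extra assessor, or change to the arms or the 560 patients is needed.

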### Sample size

The determination of the sample size was based on the following pre-experimental results for the primary outcome measure, Gastrointestinal-2: cEA, 84.8 ± 36.1 h; cTEAS, 86.8 ± 40.1 h; cTEAS+EA, 70.3 ± 39.3 h; dEA, 78.3 ± 42.2 h; dTEAS, 81.2 ± 44.2 h; dTEAS+EA, 64.1 ± 36.3 h; and control, 110.8 ± 42.3 h. PASS 15 software was used to determine the sample size of 560 patients (80 patients in each group; α = 0.05 [two-sided], β = 0.1 [90% power], with an assumed 20% dropout rate).

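### The printed allocation ratio has six terms, but the design has seven randomised arms of 80, so the ratio as written cannot produce the stated trial

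*Protocol article*

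**What the plan says.** The Randomization and blinding section is the article's only account of how the allocation sequence is produced. It reads: "The randomization sequence and allocation ratio (1:1:1:1:1:1) will be generated using the statistical software SPSS 26.0". The same section says that allocation is concealed in opaque envelopes, handed out in sequence after enrolment.

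The rest of the article has seven arms:

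- **Abstract, Methods and analysis:** patients are to be "randomly allocated to receive one of the following seven interventions". The list that follows ends with "dilatational wave TEAS, dilatational wave TEAS + EA, and a control", so control is one of the randomised options.
- **Intervention:** separate subsections describe cEA, cTEAS, cTEAS + EA, dEA, dTEAS, dTEAS + EA and control.
- **Sample size:** planning means and SDs are given for seven groups, and the result is "the sample size of 560 patients (80 patients in each group".

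No section says that any arm is filled outside the random sequence.

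**The concern.** The number of terms in an allocation ratio is the number of arms in the sequence. Six terms define a six-arm sequence, while the trial described everywhere else has seven arms. The mismatch is in the rule from which the list and envelopes are made, so it matters more than a slip in background text.

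If the list was built as printed, one arm would have no codes. Either that arm would receive no patients, or its patients would be assigned by some route other than the random sequence. Any comparison with it would then lack the protection of randomisation, and nothing in the Statistical analysis section could restore that.

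**Working it through.** **Inputs**

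- Ratio terms: 6 (Randomization and blinding).
- Randomised arms: 7, control included (Abstract; Intervention; Sample size).
- Total N = 560, with 80 per group (Sample size).
- Error rates and dropout: "α = 0.05 [two-sided], β = 0.1 [90% power], with an assumed 20% dropout rate" (Sample size).
- Planning values: "cEA, 84.8 ± 36.1 h; cTEAS, 86.8 ± 40.1 h; cTEAS+EA, 70.3 ± 39.3 h; dEA, 78.3 ± 42.2 h" and "dTEAS, 81.2 ± 44.2 h; dTEAS+EA, 64.1 ± 36.3 h; and control, 110.8 ± 42.3 h" (Sample size).

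**Step 1. The plan's own total.** Arms × number per arm = 7 × 80 = 560. This agrees with the stated total.

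**Step 2. Does the 80 per group itself make sense?** The article does not name the formula, so the basis here is inferred. Take the smallest active-versus-control difference, cTEAS against control:

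- Difference = 110.8 − 86.8 = 24.0 h.
- SD² = (40.1² + 42.3²)/2 = (1608.01 + 1789.29)/2 = 1698.65, so SD = 41.2 h.
- n = 2 × (1.960 + 1.282)² × SD²/difference² ≈ 2 × 10.51 × 1698.65/576 ≈ 62 per group.
- After 20% dropout: 62/(1 − 0.20) = 77.5, rounded up to 78.

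This is within 2 patients of 80. A one-way ANOVA over all seven groups gives 23 per group (29 after dropout), and an ANOVA over the six active arms gives 70 (88 after dropout). Neither reproduces 80. The figure of 80 is therefore plausible as it stands, and control is among the groups that were planned for.

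**Step 3. What the printed ratio gives.**

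| Reading | Per arm | Arms in sequence | Patients in sequence |
|---|---|---|---|
| Seven equal terms, N = 560 | 560/7 = 80 | 7 | 560 |
| Six equal terms, N = 560 | 560/6 = 93.3 | 6 | 560 |
| Six equal terms, 80 per arm | 80 | 6 | 6 × 80 = 480 |

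Only the first row matches the article. The second gives a fractional arm size and no seventh arm. The third leaves 560 − 480 = 80 patients, one whole arm, outside the sequence.

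**Step 4. Reach of the error if it was carried into the list.** Seven arms give 7 × 6/2 = 21 pairwise comparisons. Any one arm takes part in 6 of them, so an omitted arm affects 6 of 21, whichever arm it is.

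**The case against.** The strongest reply is that the article settles the matter itself. The abstract, the seven group descriptions, the seven sets of planning values and 7 × 80 = 560 all agree, and only one parenthesis differs. Every term in it is 1, so equal allocation is not in doubt and one term has simply been dropped. On that view the arms, the sample size and the analysis are unchanged, and harm would need a further undocumented step: staff filling an arm for which no envelopes existed.

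Much of this stands. A dropped term is the likeliest explanation, and the intended ratio is clear. What does not follow is that the point can be ignored. The wrong figure is in the generating rule, and the article gives no other description of the list against which to check it.

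Two stronger readings are tempting, and the documents support neither.

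- **That control was the arm left out.** The six active arms form a natural set of three modalities by two waveforms, so a reader might infer this. No section says so, and the abstract lists control among the randomised interventions.
- **That the active-versus-control comparisons would be the only ones with the stated power, so the error strikes the whole powered part of the trial.** The Sample size section ties the 90% to no particular contrast. With 80 × 0.8 = 64 evaluable per arm and an unadjusted two-sided 0.05 t-test, cTEAS against dTEAS + EA (86.8 − 64.1 = 22.7 h) has about 91.5% power. That is slightly more than the 90.5% for cTEAS against control. Most active-versus-active contrasts do fall below 90%, but control contrasts are not the only ones that reach it.

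**Conclusion.** The text is wrong as written. A six-term ratio cannot yield seven randomised arms of 80: it gives 93.3 per arm, or 480 patients instead of 560. This is certain from the article's own figures and rests on no assumption.

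The consequence for the trial is conditional. If the sequence was generated literally from the printed ratio, one unspecified arm would have no randomised allocation, and 6 of the 21 pairwise comparisons would not be randomised. The article does not show that this happened. If the list holds seven codes, the error is confined to the text. The sample size is unaffected in either case.

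**What to change.** 1. In the Randomization and blinding section, correct the ratio to 1:1:1:1:1:1:1.
2. Confirm from the SPSS sequence and the envelope record that all seven codes are present with 80 each. The Recruitment section ends the conduct period on 31 March 2023 and the article does not show current status, so the check should cover the list as generated or as used.
3. If a code is missing, report it, describe how patients entered that arm (if any did), and treat comparisons with it as non-randomised.

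The cost is one corrected line and one check of the list and envelopes. If the list is right, the correction closes the matter.

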### Intervention

Each group will receive an Enhanced Recovery After Surgery (ERAS)-standardized perioperative management (20). The acupoints used in the treatment group are referenced from the China National Standard Nomenclature and Location of Meridian Points (GB 12346-2021) (21). The selected acupoints and their locations are shown in Figures 2–4. The Hwato SDZ-V (Suzhou Medical Supplies Factory) EA apparatus will be used, and the current intensity will be adjusted to the tolerance level of the patient. Each treatment will last for 30 min and the initial session will commence on the first postoperative day. Treatment sessions will be provided once daily in the morning until the patient regains spontaneous flatus and can tolerate oral intake of solid food. All acupuncture maneuvers will be performed independently by the same acupuncturist, who has at least 5 years of work experience. The acupuncturist will not be replaced at any point during the study.

**Figure 2 F2:**
[figure not shown]
Localization of abdomen acupoints and electrode connection. ST21 (Liangmen) in the upper abdomen, 4 cun above the navel and 2 cun from the anterior midline. SP15 (Daheng) in the ventral part, 4 cun from the navel. A set of electrodes is attached at the blue dot (transcutaneous electrical acupoint stimulation).

**Figure 3 F3:**
[figure not shown]
Location of upper extremity acupoints and electrode connection. PC6 (Neiguan) on the volar aspect of the forearm, 2 cun on the wrist crease, and between the palmaris longus tendon and the flexor carpi radialis tendon. LI4 (Hegu) between the first and second metacarpals, at the midpoint of the radial aspect of the second metacarpal. A set of electrodes is attached at the red dot (electroacupuncture).

**Figure 4 F4:**
[figure not shown]
Location of lower extremity acupoints and electrode connection. ST36 (Zusanli) on the lateral lower leg, 3 cun under the external knee eye. ST37 (Shangjuxu) on the lateral lower leg, 6 cun under the external knee eye and 3 cun under the ST36 (Zusanli) acupoint. ST39 (Xiajuxu) on the lateral lower leg, 9 cun under the external knee eye. A set of electrodes is attached at the red dot (electroacupuncture).

#### Continuous wave EA (cEA) group

EA will be used to stimulate the bilateral Neiguan (PC6), Hegu (LI6), Zusanli (ST36), Shangjuxu (ST37), and Xiajuxu (ST39). The current frequency will be a continuous wave at 2 Hz.

#### Continuous wave TEAS (cTEAS) group

TEAS will be used to stimulate the bilateral Liangmen (ST21) and Daheng (SP15). The current frequency will be a continuous wave at 2 Hz.

#### cTEAS + EA group

EA will be used to stimulate the bilateral Neiguan (PC6), Hegu (LI6), Zusanli (ST36), Shangjuxu (ST37), and Xiajuxu (ST39). TEAS will be used to stimulate the bilateral Liangmen (ST21) and Daheng (SP15). The current frequency will be a continuous wave at 2 Hz.

#### Dilatational wave EA (dEA) group

EA will be used to stimulate the bilateral Neiguan (PC6), Hegu (LI6), Zusanli (ST36), Shangjuxu (ST37), and Xiajuxu (ST39). The current frequency will be a dilatational wave at 2/50 Hz.

#### Dilatational wave TEAS (dTEAS) group

TEAS will be used to stimulate the bilateral Liangmen (ST21) and Daheng (SP15). The current frequency will be a dilatational wave at 2/50 Hz.

#### dTEAS + EA group

EA will be used to stimulate the bilateral Neiguan (PC6), Hegu (LI6), Zusanli (ST36), Shangjuxu (ST37), and Xiajuxu (ST39). TEAS will be used to stimulate the bilateral Liangmen (ST21) and Daheng (SP15). The current frequency will be a dilatational wave at 2/50 Hz.

#### Control group

Only ERAS-standardized perioperative management, without TEAS or EA, will be performed in the control group.

All acupoints will be routinely disinfected. The acupoints in the distal limb will be punctured straight through the skin to a depth of 25–30 mm using disposable stainless steel needles (0.25 × 40 mm, Suzhou Jiajian, Jiangsu, China). The needle will then be twisted slightly to achieve the de qi sensation, and the EA apparatus will be connected with a set of electrodes in the ipsilateral Neiguan (PC6), Hegu (LI4), Zusanli (ST36), and Xiajuxu (ST39). The abdominal acupoints will be stimulated with a self-adhesive electrode sheet with electrical conductivity, and the ipsilateral Liangmen (ST21) will be connected with a set of electrodes at Daheng (SP15).

